## Methods

This protocol is reported in line with the Standard Protocol Items: Recommendations for Interventional Trials (SPIRIT) guidelines
^
34
^.

The primary aim of this study is to investigate the safety of enhanced antimicrobial therapy including increased dose RIF and LZD with or without adjunctive ASA added to standard therapy for TBM in HIV-1 infected adults.

The secondary aims are:

a.To determine CSF
*M.tb* culture positivity and Gene Xpert® Ultra positivity at baseline and at 3 and 28 days post treatment by allocation.b.To evaluate the effect of ASA and enhanced TB treatment on the incidence of immune reconstitution inflammatory syndrome (IRIS) in participants starting ARTc.To evaluate the effect of high dose RIF and LZD with and without ASA on CNS imaging (CT, MRI and MR Spectroscopy) in conjunction with clinical, immunological and transcriptional profiling.d.To determine i) whether host genotype, including leukotriene A4 hydrolase (LTA4H) genotype, influences therapeutic effect of ASA in HIV-TBM and ii) the pharmacogenetic influence on RIF and LZD exposures and toxicity.

Three sub studies will recruit all consenting participants with the following aims:

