Neutropenia (LZD)	Neutrophils	New Grade 3	Discontinue study drug. Monitor white cell count (WCC) every week. Restart at 50% dose once neutrophil count 0.5 x 109 cells/L.
		New Grade 4	Discontinue study drug permanently. Consider therapy with GM-CSF. Monitor WCC every 1 – 2 days.
Thrombocytopenia (LZD)	Platelet (Plt) count	New Grade 3	Discontinue study drug (plus any other myelosuppressive drugs as appropriate). Monitor Plt count twice weekly. Restart at 50% dose once Plt count > 50 x109 cells/L.
		New Grade 4	Discontinue study drug permanently. Consider hospital admission and/or transfusion pooled Plts. Re-test every 1 - 2 days.
Peripheral Neuropathy (LZD)	Full neurological history and examination, Brief Peripheral Neuropathy Score (BPNS) and Modified Total Neuropathy Score (mTNS)	Change in clinical history of examination resulting in: I) 1 grade increase in BPNS ii) 2 grade change in any modality on mTNS	Review with a view to discontinuing study drug (plus any other neuropathic drugs like INH). Consider restarting at 50% dose once completely resolved.
Optic Neuropathy (LZD)	14-plate Ishihara Test, visual acuity measured by logMAR chart	Change in score of 2 on 14-plate Ishihara Colour Test or new or worse logMAR score of 0.2	Stop study drug and EMB and refer for formal ophthalmological assessment. If assessment consistent with optic neuritis do not restart drug.

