**Secondary study endpoints are:**

• Death and severe disability (Modified Rankin Scale Grade 5) at 56 days (
Box 1).

**Table T5:** Box 1. Modified Rankin score

**SCORE**	**DESCRIPTION**
0	No symptoms
1	No significant disability. Able to carry out usual activities, despite some symptoms.
2	Slight disability. Able to look after own affairs without assistance, but unable to carry out all previous activities.
3	Moderate disability. Requires some help, but able to walk unassisted.
4	Moderately severe disability. Unable to attend to own bodily needs without assistance, and unable to walk unassisted.
5	Severe disability. Requires constant nursing care and attention, bedridden, incontinent.
6	Dead

• Death at 56 and 180 days.

• Disability at 56 and 180 days, stratified by baseline MRC grade.

• Grade 3 or 4 AE.

• Permanent discontinuation of experimental drugs.

• Severity and frequency of haematologic and neurologic AE related to LZD use.

• Severity and frequency of major bleeding (gastrointestinal and intracerebral) related to ASA use.

•
*M. tb* culture status and time to positivity in automated liquid culture (MGIT) and Gene Xpert® Ultra cycle threshold (C
_t_) values at days 28 and 56.

• The occurrence of TBM-IRIS assessed by the modified International Network for the Study of HIV-associated IRIS (INSHI) criteria
^
35
^.

• MRI and CT changes at day 56.

Study participants for LASER TBM must be adults (aged 18 years or over), with proven HIV-1 seropositivity, and a diagnosis of TBM meeting criteria for ‘possible’, ‘probable’ or ‘definite’ as per the published consensus definition
^
36
^.

Potential participants will be excluded if they meet any of the exclusion criteria outlined in
Box 2.

Box 2. Eligibility criteria

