**Blood**								
Weight		x	x	x	x	x	x	
Haematology: FBC and white cell differential								
Biochemistry: Creatinine, eGFR, electrolytes, LFTs	x		x	x	x	x	x	
INR	x		x			x		
HIV-1 ELISA +/- HIV Rapid Test (x2) if required	x							
CD4+ count, HIV Viral Load		x						
Plasma for PK sub-study (sparse sampling)						x	x	
Plasma for PK sub-study (intensive sampling – if consented)			x					
Stored plasma for immunological, proteomic and metabolomic profiling		x	x	x	x	x	x	
PBMC for storage		x	x			x		
Whole blood for RNA extraction		x	x	x	x	x	X	
Whole blood for DNA extraction (if consented)		x						

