**Cerebrospinal Fluid Analysis**								
Cell count, MC+S, TB culture, GeneXpert Ultra (inc Rif resistance)			x			x		
Biochemistry: protein and glucose			x			x		
Stored CSF for immunological, cellular, proteomic and metabolomic profiling;			x			x		
CSF for RNA extraction								
CSF for PK sub-study			x			x		

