### Cerebrospinal fluid analysis

CSF will be obtained via lumbar puncture at Days 3 and 28, in accordance with a detailed SOP. CSF collected for diagnosis in routine care (baseline) will be retrieved where possible. Routine microbiology, cell count, and biochemistry will be done in NHLS laboratory according to local SOPs. Samples for non-clinical testing (RNA sequencing, metabolomic and proteomic analysis and immunological assays) will be collected and transported to the IDM at UCT for processing and storage. CSF to determine drug concentrations for the PK study will be frozen at -80 degrees immediately following collection and transported to UCT Clinical Pharmacology laboratory for storage and processing.

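### The microbiological endpoint names day 56, when no CSF is scheduled, and Table 4 marks the neuropathy scores that define a primary-endpoint event at screening only

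*Protocol article*

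**What the plan says.** **Microbiology.** The list of secondary endpoints sets culture status, MGIT time to positivity and Xpert Ultra cycle threshold "values at days 28 and 56". Secondary aim (a) in Methods asks for CSF culture and Xpert positivity "at baseline and at 3 and 28 days post treatment by allocation". The section on cerebrospinal fluid analysis states: "CSF will be obtained via lumbar puncture at Days 3 and 28, in accordance with a detailed SOP". It adds that CSF taken for diagnosis in routine care will be retrieved where possible as the baseline sample. In Table 4 the row beginning "Cell count, MC+S, TB culture, GeneXpert Ultra (inc Rif resistance" is marked at day 3 and day 28.

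**Peripheral neuropathy.** Table 1 names the objective measure as "Full neurological history and examination, Brief Peripheral Neuropathy Score (BPNS) and Modified Total Neuropathy Score (mTNS". The event is triggered by "1 grade increase in BPNS ii) 2 grade change in any modality on mTNS". The section on solicited treatment-related AE makes the Table 1 events the primary safety endpoints, counted whether or not they are attributed to a study drug. The primary endpoint is assessed at 56 days. Table 4, introduced as the list of investigations planned for each visit, has one row for BPNS and mTNS, with a single mark at screening.

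**The concern.** An endpoint needs a scheduled measurement at the time it names. For microbiology, the day-56 half of the endpoint has no specimen, while day 3 is sampled and named in the aim but absent from the endpoint. Whoever analyses the trial would have to choose the time points after the fact.

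For neuropathy, a change score needs at least one later measurement. If repeats are not fixed in advance, they depend on someone deciding to score. The section on recruitment and randomisation says that the team knows the allocation, and Table 1 attributes neuropathy to linezolid, which only arms 2 and 3 receive. Control-arm events are plausible and count equally: Table 1 itself lists isoniazid as a neuropathic drug, and Table 2 gives it to every arm. Uneven scoring could therefore distort the comparison of each experimental arm with control on the primary endpoint, and the data that the DSMB sees.

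**Working it through.** No sample size, power or error rate enters this point, so the check sets the relevant places side by side.

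**Step 1. CSF culture and Xpert time points.**

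| Place | Baseline | Day 3 | Day 28 | Day 56 |
|---|---|---|---|---|
| Secondary aim (a) | yes | yes | yes | no |
| Secondary endpoint list | no | no | yes | yes |
| Cerebrospinal fluid section | routine CSF, if retrieved | yes | yes | no |
| Table 4, CSF culture/Xpert row | no mark | yes | yes | no |

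Only day 28 is common to all four. Day 56 appears in one place and has no sample in either place that schedules sampling. The endpoint line does not itself say CSF, but the matching aim does, and no other specimen is scheduled for M. tb culture or Xpert at day 56. The Table 4 rows for CSF protein and glucose and for CSF pharmacokinetics are also marked at days 3 and 28 only. Scheduled day-56 CSF samples: 0.

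**Step 2. Rows of Table 4 that bear on neuropathy.** The table has eight visit columns.

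| Row | SCR | ENR | D3 | D7 | D14 | D28 | D56 | D180 |
|---|---|---|---|---|---|---|---|---|
| BPNS and mTNS | x | | | | | | | |
| Physical examination | x | x | x | x | x | x | x | |
| AE/SAE, adherence | | x | x | x | x | x | x | |
| Modified Rankin Score | | x | | x | x | x | x | x |

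The BPNS/mTNS row has its full eight cells, so no column shift is visible. Scheduled scorings at the five follow-up visits to day 56 (days 3, 7, 14, 28 and 56): 0 of 5. Physical examination and AE review are marked at all 5. The Modified Rankin row shows that a scale meant to be repeated is given repeated marks.

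**Step 3. Text that could supply the missing timing.** The two sections describing the neuropathy scores give none. The section on assessment of AE has new events sought at every scheduled visit but names neither score. The screening mark is explained by eligibility, since BPNS Grade 3 or above is an exclusion criterion, and it can also serve as the baseline.

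**Step 4. Share of the primary endpoint.** Table 1 lists eight event types: gastrointestinal haemorrhage, intracerebral haemorrhage, transaminitis, anaemia, neutropenia, thrombocytopenia, peripheral neuropathy and optic neuropathy. The scoring gap concerns one of these eight.

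**The case against.** On microbiology, the best reply is that this is one line in a long secondary list of a phase 2A safety trial. It changes neither the primary endpoint nor the sample size, and the aim already covers day 3. That limits its importance but does not remove the contradiction. The sampling days stand in running text as well as in the table, so a damaged table cannot explain it. Nor could Figure 1, which is not shown, undo a conflict within the text.

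On neuropathy, the reply is stronger and partly stands. Figure 1 is said to show the visit schedule and the times of endpoint data collection, and it cannot be seen. Table 4 as supplied has wholly blank rows elsewhere, so marks may have been lost. Examination and AE review take place at every visit to day 56 in all arms, and Table 1 names the two scores as the objective measure, so staff may well repeat them. What remains is that the visible row and the event definition do not agree, and no visible text reconciles them.

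A reader might infer more than the documents support:

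- **That the schedule cannot deliver the primary endpoint.** It does not visibly schedule the repeat scores, but the visits at which they could be done exist.
- **That blood counts are unscheduled because the row "Haematology: FBC and white cell differential" is blank.** The section on blood says haematology is tested at the time points in Table 4, so an empty row cannot be the plan. It is probably a loss in publication or extraction.
- **That optic neuropathy has the same fault because Table 4 has no row for colour vision or acuity testing.** A condensed article may leave this to the full protocol, which is not shown.
- **That neuropathy will be over-detected on linezolid by some stated amount.** The documents give no detection rates, so neither the direction nor the size of a bias is established.

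**Conclusion.** Two internal inconsistencies stand, with different certainty.

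1. The day-56 time point of the microbiological endpoint has no scheduled specimen in any participant: one of the two time points named. Confidence is high. It affects a secondary endpoint only.
2. Peripheral neuropathy, one of eight solicited event types in the primary endpoint, is defined by a change in scores for which the visible schedule gives no measurement after screening. Confidence is moderate, because the finding rests on one table row and assumes that neither Figure 1 nor a lost mark supplies the repeats. The consequence is a possibility of unequal ascertainment between unmasked arms, not a demonstrated bias.

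No sample size or error rate in the protocol changes.

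**What to change.** **CSF endpoint.** Restate it at baseline (where routine-care CSF is retrieved), day 3 and day 28, so that aim (a), the endpoint list, the cerebrospinal fluid section and Table 4 agree. This adds no lumbar puncture and costs one line of text.

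**Neuropathy scores.** Reconcile Table 1 with Table 4 by marking BPNS and mTNS at fixed existing follow-up visits through day 56, the same visits in all three arms. If Figure 1 or the full protocol already schedules them, correct the Table 4 row to match. Events found between visits should still count: setting them aside would discard genuine toxicity in a safety trial. The cost is a few minutes per visit.

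The article reports 52 enrolled of up to 100, so at that date up to 100 − 52 = 48 participants could still be followed under a corrected schedule. The endpoint wording can be put right for everyone before analysis.

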**Inclusion criteria**
•   Age ≥18 years•   proven HIV-1 seropositivity•   Diagnosis of ‘possible’, ‘probable’ or ‘definite’ TBM
**Exclusion criteria**
•   Rifampicin-resistant
*M.tb* detected on any clinical specimen;•   History of allergy or hypersensitivity to RIF, isoniazid, ethambutol, pyrazinamide, LZD or ASA;•   Received more than 5 days of antitubercular therapy in the 30 days prior to screening;•   Receipt of regular daily ASA or NSAID prior to TBM diagnosis•   CSF unobtainable by lumbar puncture or another procedure;•   Evidence of bacterial or cryptococcal meningitis;•   Severe concurrent uncontrolled opportunistic infection including, but not limited to, active cytomegalovirus-associated disease, Kaposi sarcoma,
*Pneumocystis jirovecii* pneumonia, HIV related or unrelated malignancy, or gastrointestinal bleeding;•   Any other form of immunosuppressive therapy, including antineoplastic and biologic agents, apart from corticosteroids;•   More than 17 weeks pregnant at baseline;•   Peripheral neuropathy scoring Grade 3 or above on the BPNS;•   Any disease or condition in which the use of the standard anti-TB drugs (or any of their components) are contraindicated. This includes, but is not limited to, allergy to any TB drug or their components;•   The presence of one or more of the following:-   Estimated glomerular filtration rate (eGFR) < 20ml/min/1.73 m2
*
-   INR > 1.4 and/or clinical evidence of liver failure or decompensated cirrhosis;-   Haemoglobin < 8.0 g/dL;-   Platelets < 50 x109 /L;-   Neutrophils < 0.5 x 109 cells/L;•   Any disease or condition in which any of the medicinal products listed in the section pertaining to prohibited medication (See
Box 1) is used and cannot be safely stopped;•   Known or suspected history of drug abuse or any other reason that is, in the opinion of investigators, sufficient to compromise the safety or cooperation of the participant.*Calculated using the Cockcroft-Gault equation; INR: International normalised ration; BPNS: Brief peripheral neuropathy score; NSAID: Non-steroidal anti-inflammatory drug.

## Recruitment, randomisation, retention and withdrawal

Recruitment will be from inpatients at the participating hospital sites in South Africa (Groote Schuur Hospital, Mitchells Plain Hospital, New Somerset Hospital and Livingstone Hospital). Suitable patients will be identified by attending ward doctors and co-investigators at each site and referred to the study staff for screening.

Participant identification numbers (PID), assigned at the screening visit, will be used throughout the study. After signing the informed consent document, eligible participants will be randomised to one of the treatment arms using a pre-generated electronic randomisation list created within Microsoft Excel prior to commencement of the study. The randomisation list will be generated and updated by the trial pharmacist who will have no direct contact with trial participants or involvement with the assessment for eligibility in the trial. The second randomisation to IV or oral RIF will take place immediately, prior to receipt of study drug, for all participants allocated to experimental arms. The trial is open-label, and regimens will not be masked therefore all study team members involved in the participants care will be aware of the study arm allocation.

All trial procedures will take place in hospital during the admission period. The decision to discharge trial participants will be made by clinical, and not trial, staff. Site-specific standard operation procedures (SOP) will be developed for trial follow up visits following discharge or referral to a stepdown facility. 

A participant will be withdrawn from the study if:

• The initial
*M.tb* strain is found to be RIF-resistant on confirmatory testing;

• HIV-1 result is found to be negative on confirmatory testing;

• An alternative diagnosis is established within 5 days of antitubercular treatment initiation which leads the treating physician to discontinue antitubercular therapy;

• Withdrawal of informed consent.

Participants who withdraw consent prior to completion of the study will not undergo any further study procedures or data collection. In such cases, consent for the use of data collected prior to withdrawal of consent will be sought from the withdrawing participants. There will be no replacement for participants withdrawn from the trial.

## Interventions

### Study drug regimens

Participants enrolled to the study will receive study drug regimens as outlined in
Table 2. Dosing of the RHZE fixed dose combination (FDC) will be according to World Health Organisation (WHO) weight bands
^
38
^. Study drugs will be given orally, either as tablets/capsules or crushed, depending on the clinical circumstances. Half of participants in experimental arms will be randomised to receive IV RIF for the first 3 days of therapy and switched to the oral formulation thereafter. Study drugs will be prescribed by trial doctors, packaged and distributed by trial pharmacists.

**Table 2. T2:** Details and dosing of study drug regimen - provided for 56 days post randomisation.

	Drug					
Arm	RIF	INH	EMB	PZA	LZD	ASA
**1**	10 mg/kg O.D.	5 mg/kg O.D.	15 mg/kg O.D.	25 mg/kg O.D.		
**2**	35 mg/kg O.D.	5 mg/kg O.D.	15 mg/kg O.D.	25 mg/kg O.D.	1200 mg O.D. (28 days) then 600 mg O.D. (28 days)	
**3**	35 mg/kg O.D.	5 mg/kg O.D.	15 mg/kg O.D.	25 mg/kg O.D.	1200 mg O.D. (28 days) then 600 mg O.D. (28 days)	1000 mg O.D.

O.D.: Once daily.

### Oral RIF dosing bands

Weight based dosing to achieve equitable exposure across weight bands was based on simulations as described previously
^
39
^. These are described in
Table 3A.

**Table 3A. T3a:** Weight bands for oral rifampicin (RIF) dosing.

LASER-TBM bands	Band 1	Band 2	Band 3	Band 4	Band 5
**Weight range**	30 – 37 kg	38 – 54 kg	55– 65 kg	66 – 70	> 70 kg
**R _10_HZE (WHO)**	300	450	600	600	750
**R _25_ additional**	1200	1350	1500	1650	1950
**Total RIF (~35 mg/kg)**	1500	1800	2100	2250	2700

### Intravenous RIF

Participants allocated to experimental arms will be randomised (1:1) to receive either oral RIF 35 mg/kg or IV RIF 20 mg/kg once daily for the first 3 days of therapy (in addition to HZE and LZD with or without ASA, according to the experimental arm). Those randomised to IV RIF will receive the full RIF dose intravenously, plus additional antitubercular drugs as individual ablets (at standard doses). IV RIF will be administered as an infusion as per the package insert and according to a detailed SOP. These are described in
Table 3B.

**Table 3B. T3b:** Weight bands for intravenous rifampicin (RIF) dosing.

	Band 1	Band 2	Band 3	Band 4	Band 5	Band 6
Weight range	30 – 33 kg	34 – 37 kg	38 – 54 kg	55– 65 kg	66 – 70 kg	> 70 kg
HZE tabs	2	2	3	4	4	5
R _20_ IV	900	1050	1200	1350	1500	1650
Total RIF	900	1050	1200	1350	1500	1650

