### High dose rifampicin

Rifampicin (RIF), one of the four first line treatments for TBM demonstrates poor penetration of the blood brain barrier (BBB) with total concentrations in CSF only 10–20% of that reached in plasma
^
23
^.
*In vitro*, animal and early bactericidal activity studies suggest that the standard 600mg once daily dose is at the lower end of the dose response curve
^
24
^. This has prompted a series of studies in both pulmonary and extrapulmonary tuberculosis investigating the safety and efficacy treatment regimens containing higher doses of RIF
^
25–
32
^. None of these studies have detected a significant safety signal thereby supporting the safety of RIF up to doses of 35mg/kg. Similarly, they provide evidence to suggest superior efficacy when used at a dose of 35 mg/kg compared to 20 mg/kg
^
28,
29,
31,
32
^.

In TBM, the use of higher RIF doses is appealing given its incomplete penetration into the central nervous system. In 2013 an open-labelled randomized phase 2 study in 60 Indonesian adults with TBM showed a 50% reduction in mortality with higher dose intravenous RIF (13 mg/kg, which equates to an approximate oral dose of 20mg/kg) compared with standard dose oral therapy
^
33
^. This intensified treatment did not result in increased toxicity and was associated with a substantially lower 6-month mortality. A subsequent large randomised placebo-controlled trial in Vietnam evaluated a combined regimen of oral RIF 15 mg/kg plus levofloxacin. Unlike the previous trial using intravenous therapy (at higher equivalent oral doses of 20 mg/kg) there was no effect of mortality
^
25
^. These results, plus evidence from pre-clinical studies and pulmonary TB, provide adequate justification to systematically assess the effect on outcomes in TBM with RIF doses > 20 mg/kg.

The proposed trial combines three drugs for which there is sufficient evidence to suggest adequate safety profiles and potential benefit in a condition in which there is high mortality and inadequate treatment. Their safety in combination and in the context of HIV-1 co-infection requires careful evaluation in a controlled Phase II trial before this regimen can be tested in the context of a phase III clinical trial.

Our primary hypothesis is that increased dose RIF plus LZD and ASA can be safely added to standard therapy for HIV-1-associated TBM.

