### Sub study 1 (
*Pharmacokinetic-pharmacodynamic*)

1. To describe the plasma and CSF PK of LZD and high dose RIF.

2. To evaluate the relationship between drug exposures, toxicity and efficacy.

3. To compare exposures between intravenous and oral RIF administration.

4. To investigate the impact of high dose RIF on LZD availability.

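### The IV rifampicin dose stated as 20 mg/kg does not match Table 3B, which gives 20.8 to 31.6 mg/kg at every weight from 30 to 70 kg

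*Protocol article*

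**What the plan says.** The section Intravenous RIF sets the second randomisation as "oral RIF 35 mg/kg or IV RIF 20 mg/kg once daily for the first 3 days of therapy". The same pair of doses appears in Study design, recruitment and duration (text below Figure 1) and in the Figure 2 legend. The IV group takes no additional oral rifampicin on those days: "Those randomised to IV RIF will receive the full RIF dose intravenously". The total is therefore the IV dose.

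Table 3B has these weight bands: "30 – 33 kg 34 – 37 kg 38 – 54 kg 55– 65 kg 66 – 70 kg > 70 kg". Its dose row in mg reads "R _20_ IV 900 1050 1200 1350 1500 1650", with no approximation mark.

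Table 3A is the oral counterpart, with bands "30 – 37 kg 38 – 54 kg 55– 65 kg 66 – 70 > 70 kg" and totals of 1500, 1800, 2100, 2250 and 2700 mg. Its total row is marked as approximately 35 mg/kg, and its section gives a reason for the bands: "Weight based dosing to achieve equitable exposure across weight bands was based on simulations as described previously". The IV section gives no such reason.

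The comparison is an aim of Sub study 1: "To compare exposures between intravenous and oral RIF administration". The strategic-aim paragraph at the end of the Sub study 3 section says these PK data inform the planned phase 3 trial. It also says recruitment may stop early once the PK endpoints are met.

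**The concern.** Weight bands always make delivered mg/kg vary around a nominal figure. The usual pattern is that lighter people in a band get more than the label and heavier people less. In Table 3B the deviation runs one way over the whole range from 30 to 70 kg, so 20 mg/kg is not a typical or central value for the regimen.

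This matters because the result of interest is the exposure from one route set against the other. The phase 3 team will read that result together with a dose. If it is reported as 20 mg/kg IV versus 35 mg/kg oral, an exposure produced by 24 mg/kg in a 50 kg adult is attributed to 20 mg/kg, and the relation between the two routes is described with a ratio that the tables never deliver.

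**Working it through.** **Inputs.** Band limits and mg doses come from Tables 3A and 3B. The nominal doses of 20 and 35 mg/kg come from the section Intravenous RIF.

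**Formulas.** Delivered mg/kg = band dose / body weight. The weight at which the label is met = band dose / 20. IV:oral ratio = Table 3B dose / Table 3A dose at the same weight. The nominal ratio is 20/35 = 0.571.

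| Weight (kg) | IV mg | mg/kg at lower limit | mg/kg at upper limit | Weight giving 20 mg/kg | Oral mg | IV:oral | Relative to 0.571 |
|---|---|---|---|---|---|---|---|
| 30–33 | 900 | 30.0 | 27.3 | 45.0 | 1500 | 0.600 | +5% |
| 34–37 | 1050 | 30.9 | 28.4 | 52.5 | 1500 | 0.700 | +23% |
| 38–54 | 1200 | 31.6 | 22.2 | 60.0 | 1800 | 0.667 | +17% |
| 55–65 | 1350 | 24.5 | 20.8 | 67.5 | 2100 | 0.643 | +13% |
| 66–70 | 1500 | 22.7 | 21.4 | 75.0 | 2250 | 0.667 | +17% |
| >70 | 1650 | 23.2 (at 71) | open | 82.5 | 2700 | 0.611 | +7% |

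**The stated figure is not reproduced.** In each of the five closed bands, the weight that would give 20 mg/kg lies above the band's upper limit. The smallest value is 1350/65 = 20.8 (4% above 20) and the largest is 1200/38 = 31.6 (58% above). All 41 whole-kg weights from 30 to 70 exceed 20, and only 6 of them (62–65, 69 and 70 kg) lie within 10% of it.

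**Does rounding explain it?** All IV doses are multiples of 150 mg. Take 20 mg/kg at the upper limit of each band and round up to the next 150 mg:

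- 20 × 54 = 1080, giving 1200
- 20 × 65 = 1300, giving 1350
- 20 × 70 = 1400, giving 1500

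These three match the table. For the two lowest bands, 20 × 33 = 660 and 20 × 37 = 740 both give 750, whereas the table has 900 and 1050. No single rounding rule of this kind reproduces Table 3B.

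**The oral table, for contrast.** Delivered oral mg/kg is 50.0–40.5 (30–37 kg), 47.4–33.3 (38–54 kg), 38.2–32.3 (55–65 kg) and 34.1–32.1 (66–70 kg). Of the 41 whole-kg weights, 27 are above 35, 13 are below and one equals it. From 47 to 70 kg all lie within 10% of 35.

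**Effect on the comparison.** Suppose exposures were scaled by the nominal doses. The IV/oral result would be multiplied by 35/20 = 1.75, where the delivered doses give 1.43 (1500/1050) to 1.67 (1500/900). The scaled ratio would then be too high by 1.75/1.67 = 1.05 to 1.75/1.43 = 1.23 times. At 50 kg the delivered ratio is 1800/1200 = 1.50, so the factor is 1.17.

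**The case against.** The strongest reply is that mg/kg figures in this article are names of regimens. Table 2 lists plain mg/kg doses even though the accompanying text says the fixed-dose combination follows WHO weight bands. In Table 3A the R_25 row gives 1200/30 = 40.0 mg/kg at 30 kg, 60% above its name, and 1500/65 = 23.1 at 65 kg. The R_10 row runs from 300/37 = 8.1 to 450/38 = 11.8. This stands as far as it goes: a label without an approximation mark is not in itself an error here. But the R_10 and R_25 rows fall on both sides of their names between 30 and 70 kg, and the R_20 row does not.

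A second reply is that the IV bands may be deliberate. The section High dose rifampicin equates 13 mg/kg IV with about 20 mg/kg oral, a ratio of 0.65, which lies inside the tabulated 0.60 to 0.70. That is possible, but the article does not say so, and 0.65 is not the labelled ratio either.

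Third, the extremes overstate the effect on the route comparison. Both routes run high at low weight, so the relevant size is the 5 to 23% shift in the dose ratio and not the 58% at 38 kg. This is correct.

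Fourth, the PK analysis is left to the statistical analysis plan, which is not shown. Its scaling method therefore cannot be criticised here. The conflict between the stated dose and the table is printed in the article itself.

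**Conclusion.** The IV dose stated as 20 mg/kg does not describe the regimen in Table 3B. The delivered dose is 20.8 to 31.6 mg/kg over 30 to 70 kg, and the IV:oral dose ratio is 5 to 23% above the nominal 0.57. This should be corrected because the route comparison informs the phase 3 trial.

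Three stronger readings are tempting and are not supported:

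- **That the oral bands are wrong because they reach 50 mg/kg.** That value occurs only at 30 kg. The table is marked approximate, it is declared to rest on simulated exposure, and its doses fall on both sides of 35.
- **That lighter participants are dosed beyond what the article says is safe.** The section High dose rifampicin cites earlier studies as "thereby supporting the safety of RIF up to doses of 35mg/kg". It does not say that support ends there. Whether that figure is an exact or a banded nominal dose depends on sources not shown.
- **That the IV–oral comparison is invalid.** Participants are randomised between two defined sets of mg doses, and that contrast stands whatever the sets are called.

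The figures assume whole-kg bands as printed and 71 kg as the start of the open band. The article gives no weight distribution, so the share of participants at each deviation cannot be computed. The 1.05 to 1.23 factor applies only if someone scales by the nominal doses.

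**What to change.** The sponsor should reconcile the 20 mg/kg statements (text below Figure 1, Figure 2 legend, section Intravenous RIF and the R_20 row) with the mg doses in Table 3B, and state the basis of the IV bands. This review does not say which should change.

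The PK report should then do the following:

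- Tabulate delivered mg and mg/kg by weight band and route.
- Word the IV-versus-oral conclusion in delivered dose.
- Keep the comparison of exposures under the two banded regimens as it is. A dose-normalised comparison may be added as supplementary. It answers a different question and assumes that exposure is proportional to dose.

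The study status section reports 52 participants already enrolled, so the delivered-dose table is needed however the label is settled.

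The cost is a short protocol clarification and one descriptive table. Weight is scheduled at enrolment and day 3, which with the band gives the assigned mg. The article mentions witnessed intake at intensive sampling and adherence monitoring, but does not state that administered mg is recorded for each dose. That should be confirmed first.
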